## Statistical methods and data analysis

Data will be analyzed by using SAS (version 9.2; SAS Institute, Inc., Cary, NC, USA) and SPSS (version 17, SPSS Inc., Chicago, IL, USA), accordingly. Demographic data will be examined differences between groups by using chi-square test (for categorical variables) and Wilcoxon rank sum test (for continuous variables).

Time-to-event outcomes, such as FFLP (time to in-field target-tumor progression), progression-free (time to local, regional, or distance progression) and overall survival (time to patient death from any cause) will be evaluated by using Kaplan-Meier method. Curve difference between groups will be assessed by using log-rank test. Multivariate analysis will be done by using Cox proportional hazard regression. Hazard ratio with 95% confidence interval will be provided in conjunction with *p* values to demarcate effective size. All statistical analysis will be performed by using a two-tailed approach. A *p* value of < 0.05 will be considered as having a statistical significance.

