**Methods:**

The present study is an open-label, parallel, randomized controlled trial. A total of 120 patients will be included into two study groups, i.e., SABR and re-TACE, with a 1:1 allocation rate. A 3-year allocating period is planned. Patients with incomplete response after initial TACE will be enrolled and randomized. The primary endpoint is 1-year freedom-form-local-progression rate. Secondary endpoints are disease-progression-free survival, overall survival, local control, response rate, toxicity, and duration of response of the treated tumor.

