## Outcome measures

### Primary outcome measure

The primary outcome measure is freedom from local progression (FFLP) [24]. FFLP will be defined as time with no in-field progressive disease. Response for target lesions will be defined according to the RECIST version 1.1 and modified RECIST (mRECIST) [52]. The target lesions should show intra-tumor arterial enhancement on contrast-enhanced CT or MRI and can be accurately measured in at least one dimension as 1 cm or more [53, 54].

Several tumor responses will be defined by two independent physicians (one hepatic-specific radiologist and one radiation oncologist): complete response (CR), total disappearance; partial response (PR), 30% decrease in single longest diameter (SLD) of contrast-enhanced part; stable disease (SD), neither partial response nor progressive disease met; and, progressive disease (PD), 20% increase of SLD or new lesion(s).

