### Secondary outcome measure

Several secondary outcomes will be measured at 1 and 2 years, as follows: (1), overall survival; (2), progression-free survival; (3), tumor response rate; and (4), toxicity. Post-intervention complete or partial response will be defined as having a tumor response. Treatment-associated toxicity will be classified according to CTCAE, v.4.03 [55]. Toxicity within 3 months after initiation of interventions will be recorded as acute toxicity. And, toxicity that developed after 3 months will be considered as late toxicity. Liver-specific toxicity including classic and non-classic radiation-induced liver disease (RILD) will also be assessed. Degree of toxicities will be documented, such as ascites (i.e., absent, mild to moderate, and severe/refractory) and encephalopathy (i.e., absent, mild [I-II], and severe [III-IV]).

Several image and laboratory studies will be conducted for assessing treatment response and toxicities. First, CT, MRI, or abdominal sonography will be done per 3 months within the first two-year follow-up, then per 6 months thereafter for another 3 years. Second, specific laboratory studies will be followed up regularly, such as AST, ALT, and Bilirubin (both total and direct; Table 1). All adverse and potential harming events will be systemically collected and then analyzed in investigator meetings. Severe adverse events will be reported to IRB within 2 weeks as the IRB-monitoring guideline.

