## Discussion

### SABR has been reported as an effective modality in all-stage HCC patients, but evidence from phase-III randomized trials is largely lacking

For patients with intermediate stage of BCLC classification, most patients received TACE as their local-regional therapies. However, TACE alone seldom achieves satisfactory complete response and demonstrates a dismal 5-year survival rate of < 20% [56]. Recently, modern high-dose SABR achieves 60–100% tumor response rate when combined with TACE [11 17–22]. Phase I and II trials also showed promising results of SABR on local control (1-year, 87%; 2-year, 94.6%) and survival rate (1-year, 55%; 2-year, 68.7%) [24, 25]. Thus, based on these results, SABR has been suggested as an effective modality for HCC patients with early-stage lesions [19, 24, 57, 58], unresectable tumors (i.e., ≤10 cm) [59], and post-TACE residual tumor [20, 44]. However, level 1 evidence from randomized trials for liver SABR is largely lacking.

A lack of level-III evidence is the main barrier for recommending SABR as a standard of care in most international treatment guidelines. As a result, conducting randomized trials to demarcate the role of SABR in HCC patients is warranted, especially in the Asia-Pacific region, where HBV- and HCV-related HCCs are predominated [2, 3].

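### The secondary endpoint named progression-free survival is defined without death as an event, so as written it is time to progression

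*Protocol article*

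**What the plan says.** The endpoint is named in two places. The Abstract (Methods) states: "Secondary endpoints are disease-progression-free survival, overall survival, local control, response rate, toxicity, and duration of response of the treated tumor". The Secondary outcome measure section lists "progression-free survival; (3), tumor response rate", to be measured at 1 and 2 years, and gives no event definition.

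The events are given only in Statistical methods and data analysis, in one sentence covering three time-to-event outcomes:

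- freedom from local progression: "FFLP (time to in-field target-tumor progression";
- the progression-free endpoint: "progression-free (time to local, regional, or distance progression";
- overall survival: "overall survival (time to patient death from any cause".

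All three are to be estimated by Kaplan-Meier and compared by log-rank test, with Cox regression for hazard ratios. The article does not say how a death without progression is handled in the first two.

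**The concern.** Progression-free survival conventionally means alive and without progression, so its events are progression or death from any cause, whichever comes first. The event list here has only progression. Because the same sentence does name death for overall survival, the text gives no hint that death was meant to be understood for the progression-free endpoint too.

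Three things follow. The reported rate will be higher than a PFS that counts death. An arm that loses more patients before progression will not show it on this endpoint. The result will not be comparable with PFS elsewhere, including the progression-free result of another randomised trial that the article itself cites in its Conventional radiotherapy section.

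Death before progression is foreseeable here: the trial admits Child-Pugh B patients with bilirubin up to 3.0 mg/dl and lists radiation-induced liver disease among the toxicities to be assessed. The article does not say how often such deaths are expected.

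**Working it through.** No figure in the article depends on this definition, so there is nothing to reproduce. The check compares the texts and then illustrates the size.

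**1. Name against definition**

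| Place | Name | Events |
|---|---|---|
| Abstract, Methods | disease-progression-free survival | none given |
| Secondary outcome measure | progression-free survival | none given |
| Statistical methods and data analysis | progression-free | local, regional or distant progression |
| Same sentence | overall survival | death from any cause |

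The name carries survival. The event list does not.

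**2. Effect on the reported rate**

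Inputs:
- Survival from the first subsection of the Discussion: "survival rate (1-year, 55%; 2-year, 68.7"%. The 2-year figure exceeds the 1-year figure, so the two cannot lie on one survival curve. They are used only as two alternative settings.
- A nominal 1-year progression-free rate of 50%, chosen for illustration.
- Assumptions: constant hazards, and death independent of progression. The share k of the overall death hazard that acts before progression is not given, so it is set to 0.5 and to 1.

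The 68.7% is a 2-year figure and must be brought to 1 year: √0.687 = 0.829.

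Formula: PFS with death counted = 0.50 × S^k, where S is 1-year survival.

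| S at 1 year | k = 0.5 | k = 1 |
|---|---|---|
| 0.55 | 0.50 × 0.742 = 37% | 0.50 × 0.55 = 28% |
| 0.829 | 0.50 × 0.910 = 46% | 0.50 × 0.829 = 41% |

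So a nominal 50% corresponds to 37–46% (k = 0.5) or 28–41% (k = 1). With no deaths before progression the gap is zero.

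**3. Effect on the comparison**

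All hazards in this step are assumed, not taken from the article. Let progression be 0.5 per year in both arms, and death before progression 0.3 per year in one arm and 0.1 in the other.

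- As defined: hazard ratio 0.5/0.5 = 1.00, and exp(−0.5) = 60.7% at 1 year in both arms.
- With death counted: hazard ratio (0.5 + 0.3)/(0.5 + 0.1) = 1.33; exp(−0.8) = 44.9% against exp(−0.6) = 54.9%.
- Deaths before progression in year 1, with 60 per arm: 60 × (0.3/0.8) × (1 − 0.449) = 12.4, against 60 × (0.1/0.6) × (1 − 0.549) = 4.5.

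The definition as written would miss that difference. With death hazards of 0.2 and 0.1 the hazard ratio with death counted is 0.7/0.6 = 1.17. With equal death hazards it is 1.00, and the comparison between arms is not affected.

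**4. Does the same criticism reach FFLP?**

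Under the step 3 hazards with independent deaths, treating deaths as censored leaves Kaplan-Meier FFLP at 60.7% in both arms, although one arm has three times the death hazard. In the arm with more deaths, one minus the cumulative incidence of progression is 1 − (0.5/0.8) × (1 − 0.449) = 65.6%. The Kaplan-Meier figure is the lower of the two, so the arm is not flattered.

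A simulation with a shared frailty (gamma, shape and scale 1; 400,000 patients per scenario) made deaths informative. Tripling the death hazard from 0.1 to 0.3 then raised 1-year Kaplan-Meier freedom from progression only from 67.6% to 69.3%, while the composite with death fell from 62.5% to 55.6%.

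**The case against.** The strongest reply is that the harm is limited. This is a secondary endpoint, overall survival is analysed separately with death from any cause, and liver toxicity is assessed, so an excess of deaths in one arm would be visible in the trial. That stands, and it limits the consequence. It does not make the event list right for the endpoint named.

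It may also be said that a journal article leaves event and censoring details to a fuller document. That would excuse silence. Here the article states an event list. An analysis plan that follows it repeats the mismatch, and one that adds death contradicts the published protocol.

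It is fair, too, that the article gives no censoring rule for deaths. That such deaths would be censored follows from the event list together with Kaplan-Meier, but it is an inference.

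A reader might go further and infer that FFLP is biased in the same way, so that early deaths flatter an arm on the primary endpoint. The document does not support this. FFLP is named and defined consistently as freedom from in-field progression ("FFLP will be defined as time with no in-field progressive disease"), and leaving death out fits that name. If deaths are independent of local progression, the Kaplan-Meier curve and the cause-specific hazard ratio are unchanged. A favourable shift needs informative deaths, and it was small in the scenario tried.

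A reader might also infer that deaths before progression will be frequent in this trial. The Discussion's survival figures come from other series, cited elsewhere in the article for unresectable and oligometastatic disease. This trial enrols BCLC A–B, Child-Pugh A–B and ECOG 0–1, and no death rate is given for that group. Reading 68.7% as a 1-year figure would also exaggerate the milder end of the range.

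**Conclusion.** The mismatch is real and lies in the text itself: the endpoint is called progression-free survival and defined as time to progression. Its direction is certain wherever any patient dies before documented progression: the reported rate exceeds a PFS that counts death, and an arm with more such deaths is not penalised.

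Its size is not fixed by the document. The 37–46% and 28–41% against a nominal 50% rest on constant, independent hazards, on survival borrowed from other series, and on the assumed share of the death hazard acting before progression. They show that the gap could matter and are not a forecast for this trial.

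The point is confined to this secondary endpoint. It shows no bias in the primary endpoint and does not mean that deaths go unseen in the trial. It should be corrected before analysis.

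**What to change.** In Statistical methods and data analysis, define progression-free survival as the time to the first of local progression, regional progression, distant progression or death from any cause. If the present quantity is the one wanted, keep the event list and call it time to progression there, in the Abstract and in Secondary outcome measure.

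The cost is one sentence, or a change of name in three places. With death added, the reported PFS will be lower.

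The definition and test of FFLP need no change. A cumulative incidence of local progression with death as a competing event, shown beside the Kaplan-Meier rate, would be a useful but optional supplement.

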### Assignment of interventions: randomization and allocation

Computer-generated random numbers will be used for participant allocation. Two factors will be used as stratification factors, i.e., BCLC cancer stage and level of total bilirubin. A 2-by-2 cross table will be used for randomizing and blocking: total bilirubin (< 2 versus 2–3 g/dl) and BCLC (A versus B), with a block size of 4 in each stratification.

Opaque and sealed envelopes will be used for implementing the randomization and allocation sequence. When the participants are ready to be randomized, the study investigator will pull the very next randomization envelope by sequence from the envelope file, which will be locked in secure locker. The study nurse will record associated information on the study randomization list and the participant’s case report form. Finally, the envelope will be opened to reveal the subject’s treatment assignment and second study staff will double check the envelope file in real time to verify correct treatment assignment. An inspection of envelopes will be completed by data and safety monitoring board (DSMB) during routine monitoring visit. Note that blinding in either sides (i.e., physician or participants) cannot be done because of intervention natures.

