### Sample size calculation

According to prior studies, response rates have been reported: 38% in patients treated with TACE alone [37] and 76.6% in those treated with TACE then salvage SABR [44]. As a result, an absolute increase of 30% in response rate will be considered as having a clinical significance. By using probability of type I error (α, 0.05; and, power [1 - β], 80%), 46 patients will be required in both the two study groups, resulting in a total study cases of 92. With an estimate of drop-out rate of 20%, we will enroll an additional 24 patients to counter potential attrition, reaching a final sample size of 120.

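### Randomisation is stratified by BCLC stage and bilirubin, but the stated log-rank and Cox analyses do not mention the strata, which costs power to the extent that the factors are prognostic

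*Protocol article*

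**What the plan says.** Under the heading on assignment of interventions, the protocol article states: "Two factors will be used as stratification factors, i.e., BCLC cancer stage and level of total bilirubin". The two factors are crossed into four strata (BCLC A or B by bilirubin below 2 or 2–3), "with a block size of 4 in each stratification".

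The section on primary outcome states: "The primary outcome measure is freedom from local progression (FFLP". The statistical methods section treats FFLP, progression-free survival and overall survival as time-to-event outcomes, estimates them by Kaplan-Meier, and adds: "Curve difference between groups will be assessed by using log-rank test". It continues: "Multivariate analysis will be done by using Cox proportional hazard regression". Hazard ratios with 95% confidence intervals are to accompany the p values, and "All statistical analysis will be performed by using a two-tailed approach".

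Nowhere does the article carry the stratification factors into an analysis, and nowhere does it rule that out. It does not name the Cox covariates.

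**The concern.** Stratified blocks hold the arms close to balanced on the two factors. If a factor predicts the outcome, that balance removes a source of chance difference between the arms. A log-rank test that ignores the strata still counts this source in its variance. The test statistic is then too small on average, the true type I error falls below the nominal 5%, and power is lost.

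This matters more in a trial of 120 patients that names small sample size and type II error as its main limitation. There is also a reporting issue. The p value comes from a log-rank test, while the hazard ratio may come from a Cox model whose covariates are open, so the two may not describe the same comparison.

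**Working it through.** **The plan's own figure.** The sample size section says: "By using probability of type I error (α, 0.05; and, power [1 - β], 80%), 46 patients will be required in both the two study groups". The inputs are response rates, with a 30-point difference. Taking 46.6% versus 76.6% (mean 0.616):

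- Uncorrected: n = [1.960 × √(2 × 0.616 × 0.384) + 0.842 × √(0.466 × 0.534 + 0.766 × 0.234)]² / 0.30² = 40.06.
- Continuity-corrected: (40.06 / 4) × [1 + √(1 + 4 / (40.06 × 0.30))]² = 46.5.

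This agrees with 46 to within rounding. It is a two-proportion calculation on response, so no stated sample size depends on the form of the log-rank test.

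**The two tests.** Both use Z = U / √V. At each event, let p be the proportion of patients at risk who are in the SABR arm. Then U = Σ(observed − p) and V = Σ p(1 − p). The unstratified test takes p over all patients at risk. The stratified test takes p within each of the four strata and sums U and V over strata. The null hypothesis is rejected if |Z| > 1.96.

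**Inputs from the article:** four strata, blocks of 4, 1:1 allocation, two-sided 5%, 2-year follow-up, 120 patients, 20% dropout.

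**Assumptions, not in the article:** treatment hazard ratio 0.5, the strength of each prognostic factor, the stratum shares and the event rate. Two sets were used:

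- Set A: 120 patients with about 20% dropout as censoring, 60% BCLC B, 15% bilirubin 2–3, hazard 0.5 per year in the lowest-risk control stratum, 40,000 runs.
- Set B: 96 patients (120 × 0.8), control 1-year FFLP about 60%, 50% BCLC B, 20% bilirubin 2–3, 4,000 runs.

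| Prognostic hazard ratio | Set | True alpha, unstratified / stratified | Power, unstratified / stratified | Gain from stratifying (points) |
|---|---|---|---|---|
| None | A | 5.2% / 5.2% | 73.3% / 72.4% | −0.9 |
| BCLC only, 1.5 | A | 5.2% / 5.4% | 78.5% / 78.7% | 0.2 |
| BCLC only, 2 | A | 4.3% / 5.2% | 80.6% / 82.4% | 1.8 |
| Both, 1.5 | A | 4.8% / 5.2% | 79.8% / 80.2% | 0.4 |
| Both, 1.5 | B | – | 68% / 69% | 1 |
| Both, 2 | A | 4.0% / 5.1% | 80.7% / 84.1% | 3.4 |
| Both, 2 | B | 3.7% / 5.1% | 66% / 69% | 3 |
| Both, 3 | A | 2.6% / 5.2% | 77.0% / 87.2% | 10.2 |
| Both, 3 | B | 2.7% / 5.0% | 59% / 71% | 12 |

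Compare within rows only. In set A a stronger prognostic effect also raises the event rate, so power is not comparable down the column.

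**Simulation error.** In set A the standard error of an alpha near 5% is √(0.05 × 0.95 / 40,000) = 0.11 points, and of a power near 80% it is √(0.8 × 0.2 / 40,000) = 0.20 points. In set B the standard error of a power near 69% is √(0.69 × 0.31 / 4,000) = 0.73 points, so its 1-point difference at hazard ratio 1.5 is close to noise.

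**Stratum sizes.** If the factors are independent, set A gives the two bilirubin 2–3 strata 120 × 0.15 × 0.6 = 10.8 and 120 × 0.15 × 0.4 = 7.2 patients. Sparse strata are therefore a practical possibility.

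**The case against.** The strongest reply is that the article is a condensed account and the statistical analysis plan is not shown. Whether a log-rank test is stratified, and which covariates enter a Cox model, are often settled there. The word unstratified does not appear, and the Cox model may already include both factors. That stands as far as it goes: a reader might infer that the trial has chosen an unstratified test, but that is the ordinary reading of an unqualified log-rank, not a stated decision. The article does, however, name the test, the sidedness, the significance level and the model class, so the point concerns a stated method that does not use the stated design.

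Four stronger inferences are tempting, and the article does not support them.

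- **That power is certainly lost.** The article gives no prognostic strength for either factor and no stratum sizes. The endpoint is in-field progression, and nothing in the article shows that BCLC stage or bilirubin predicts it strongly.
- **That the test is invalid.** Where there is an effect, the type I error falls below 5%; it is not inflated.
- **That an unstratified hazard ratio is biased.** It is closer to 1 because it is a marginal rather than a within-stratum quantity, and either is a legitimate target.
- **That the sample size is wrong for this reason.** It rests on response rates.

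A rule that merely collapses strata with too few events would also add a data-dependent choice. It needs a number fixed beforehand.

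**Conclusion.** The point holds in conditional form. The design stratifies on two factors, and the stated analysis does not use them. If the test is run as written, it remains valid but is conservative to the extent that the factors are prognostic.

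Under a treatment hazard ratio of 0.5 and the assumed stratum shares and event rates, the loss is negligible at a prognostic hazard ratio of 1.5. It is moderate at 2 for both factors, and large only if both reach 3, a case for which the article offers no support. The direction is the same under both sets of assumptions.

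The balance favours stratifying: a cost of about 1 point if neither factor matters, against a gain that grows with their strength. Choosing the two factors for stratification suggests that the investigators expect them to matter. This is an improvement worth making in a small trial, not a threat to its validity.

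**What to change.** State in the analysis plan, before any comparison by arm is made, that:

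1. the log-rank tests for FFLP, progression-free survival and overall survival are stratified by the two randomisation factors, BCLC stage (A/B) and total bilirubin (below 2 / 2–3);
2. the hazard ratio and its 95% confidence interval come from a Cox model stratified by the same factors, so that the p value and the estimate refer to one comparison;
3. a numerical rule for sparse strata is set in advance and applied blind to arm, for example stratifying by BCLC stage alone if a bilirubin 2–3 stratum has fewer than a stated number of events;
4. the unstratified log-rank test is reported as a sensitivity analysis.

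The cost is wording, since both factors must be known at randomisation and no new data are needed. The ethics section also requires changes to outcome analyses to be approved again by the IRB. The statistical price is about 1 point of power if the factors are not prognostic. If the unseen analysis plan already says this, no change is needed beyond making the published description agree.

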### Inclusion criteria

Several inclusion criteria will be as follows.Patients who are diagnosed with HCC via one of the following methods:radiographically typical enhancement pattern with arterial enhancement and portal or delayed washed out on triple-phase dynamic Computed Tomography (CT) or Magnetic Resonance Imaging (MRI), with or without an elevated value of alpha-fetoprotein (AFP); or,histopathological confirmation of HCC.HCC patients who are treated with initial TACE with incomplete response (i.e., partial response, stable disease, or disease progression).Age ≥ 20 years old.BCLC stage A-B and Child-Pugh score A-B.Unresectable tumors, medically inoperable status, or refusal of surgery.Clinically feasible for SABR or re-TACE.SABR can be applied within 6 weeks of registration.ECOG 0–1.Life expectancy > 3 months. Negative pregnancy. No prior treatment, except for surgical resection and radiofrequency ablation (RFA). Criteria of allowed laboratory data were as follows:hemoglobin, ≥8.0 g/dl (may be post-transfusion if clinically indicated);total bilirubin, ≤3.0 mg/dl;AST (SGOT), ≤5-fold institutional upper limit of normal range;ALT (SGPT), ≤5-fold institutional upper limit of normal range;absolute neutrophil count, ≥1000/cumm;platelet count, ≥20,000/cumm (may be post-transfusion if clinically indicated); and,prothrombin time, international normalized ratio, ≥1.7.

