### Arm A, the experimental group: SABR (planned *n* = 60)

SABR, or alternatively named Stereotactic Body Radiotherapy (SBRT), is a rapidly developing modern radiotherapy technique for liver tumors [47, 48]. TrueBeam™ (Varian Medical Systems, CA, USA) will be used to deliver SABR by using an extremely conformal radiation dose distribution and rapid fall-off of the peripheral dose, leading to a large sparing of surrounding normal tissues.

To achieve high precision, Image-guided Radiotherapy (IGRT) with respiratory-gated or breath-holding technique will be combined with SABR to overcome the effect of positioning uncertainty and respiratory motion. Real-time Position Management™ (RPM) system (Varian Medical System, CA, USA), version 1.7.5, will be used when breath-holding technique cannot be conducted confidentially. A CT scanner will be used for simulation (Somatom Emotion 6, Siemens Medical Solution, Forchheim, Germany). These techniques have been reported to improve treatment precision of irradiating targets that are affected by respiratory motion, such as lung, breast, and liver tumors [49].

SABR will be delivered in 5 fractions within 2 weeks, and the prescription dose will be ranged from 35 to 50 Gy, depending on tumor size, location, and normal tissue constrains. In some situations, treatment course will be prolonged to 8–10 fractions, for example, patients with poor liver function (e.g., Child B8–9) or their tumor location near the adjacent gastrointestinal tract, diaphragm, or the central zone of the liver (i.e., ≤1.5 cm around the main portal vein). The preferred inter-fraction time interval will be 48 h.

No expansion from Gross Target Volume (GTV) to CTV will be performed for most irradiating targets, and margins to generate Plan Target Volume (PTV) from Clinical Target Volume (CTV) will be ≤10 mm. The prescribed isodose should encompass 95% of PTV but 100% of CTV.

Critical organ constrains will be obeyed according to RTOG 1112 protocol [50]. Briefly, the 0.5-cc maximum dose regions of normal structures will be as follows: stomach, duodenum, small and large bowels, < 30 Gy; esophagus, < 32 Gy; and, 5 mm around the spinal cord, < 25 Gy. Bilateral mean kidney dose should be < 10 Gy. Allowed mean liver dose (MLD, the mean dose to the liver minus all GTV) should be kept < 13 Gy (if prescribed dose is 50 Gy) and < 15 Gy (if prescribed dose is 40–45 Gy).

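### The unadjusted log-rank test of FFLP leaves out treated-lesion response to the initial TACE and tumour size, both known at entry; adjusting for them is a cheap gain in efficiency and precision

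*Protocol article*

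**What the plan says.** The primary endpoint is local: "FFLP will be defined as time with no in-field progressive disease" (Primary outcome measure). For its comparison, Statistical methods and data analysis says "Curve difference between groups will be assessed by using log-rank test. Multivariate analysis will be done by using Cox proportional hazard regression". It also promises an effect size: "Hazard ratio with 95% confidence interval will be provided in conjunction with" p values. It does not say which covariates enter the Cox model, whether that model is primary or supportive, or whether the reported hazard ratio is adjusted.

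The same section plans baseline testing: "Demographic data will be examined differences between groups by using chi-square test", with a Wilcoxon rank sum test for continuous variables. It gives no use for the results.

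Two entry characteristics matter here.

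- **Response to the initial TACE.** Inclusion criteria admit "HCC patients who are treated with initial TACE with incomplete response (i.e., partial response, stable disease, or disease progression").
- **Tumour size.** For SABR, "the prescription dose will be ranged from 35 to 50 Gy, depending on tumor size, location, and normal tissue constrains". In the re-TACE arm the volume of oil-based contrast also depends on size. No size limit is listed at entry beyond BCLC stage A–B.

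Randomisation is stratified by BCLC stage and total bilirubin only (Assignment of interventions). Response is itself an entry criterion, and Table 1 schedules abdominal CT or MRI at screening, so both values should be in hand before allocation.

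**The concern.** The endpoint is growth of the treated tumour. Patients enter with tumours that have just shrunk, stayed stable or grown, and with sizes that vary enough to influence how each arm is treated. It is plausible that both features predict local progression.

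If they do, a test that ignores them gives up power. An unadjusted hazard ratio also carries whatever chance imbalance in them the randomisation leaves. The protocol itself names small sample size, and the Type II error that follows from it, as its major limitation. BCLC stratification separates tumour burden only coarsely and does not capture response to the first TACE.

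The planned baseline significance tests do not help. After proper randomisation their null hypothesis is true by design, and at this sample size they pass over imbalances of practical interest.

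**Working it through.** **The plan's own figures.** The article gives no power for FFLP. Its 46 per group is for a 30-point difference in response rate (two-sided 5%, 80% power). Standard formulas for 38% v 68% give 43 without and 49 with continuity correction, so 46 is of the right order, but it says nothing about FFLP. The check below uses the planned 60 per arm.

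**1. Chance imbalance in a binary entry factor.** The share p progressing after the initial TACE is assumed; the documents give none.

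SE of the between-arm difference = √(2p(1−p)/60)

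| Assumed share | SE | Probability of a gap above 10 points, either direction |
|---|---|---|
| 20% | 0.073 | 17% |
| 30% | 0.084 | 23% |
| 40% | 0.089 | 26% |

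At a 30% share, a 10-point gap has z = 0.10/0.084 ≈ 1.2 and p ≈ 0.23. A baseline test would not flag it.

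**2. Power, log-rank v adjusted Cox.**

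- From the documents: 120 patients, 1:1, two-year follow-up, two-sided 5%.
- Assumed: exponential times; conditional HR 0.5; control 1-year FFLP 50–70%; loss of about 20% per year; response in three equally likely levels; normally distributed size; the same covariate HR per response step and per SD of size.
- Runs: 3,000 per row, Monte Carlo SE about √(0.25/3000) = 0.9 points.

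As a plausibility check, ignoring covariates, HR 0.5 turns control FFLP of 50%, 60% and 70% into 0.50^0.5 = 71%, 0.60^0.5 = 77% and 0.70^0.5 = 84%. The article's Background cites 72–89.8% for SABR local control at one year.

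| Control 1-year FFLP | Covariate HR | Mean events | Log-rank | Adjusted Cox | Gain (points) |
|---|---|---|---|---|---|
| 50% | 1.3 | 62.5 | 74.7% | 76.5% | 1.8 |
| 50% | 1.5 | 62.0 | 71.0% | 77.6% | 6.6 |
| 50% | 2.0 | 60.8 | 55.9% | 76.0% | 20.1 |
| 60% | 1.3 | 51.5 | 65.3% | 67.5% | 2.2 |
| 60% | 1.5 | 51.1 | 61.4% | 66.6% | 5.2 |
| 60% | 2.0 | 50.1 | 51.8% | 66.8% | 15.0 |
| 70% | 1.3 | 39.8 | 55.4% | 56.1% | 0.7 |
| 70% | 1.5 | 39.5 | 53.7% | 57.0% | 3.3 |
| 70% | 2.0 | 38.5 | 43.8% | 53.2% | 9.4 |

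A second simulation (1,500 runs) coded response as progression v other and took control 1-year FFLP of 60–65%.

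- Weak (size HR 1.3 per SD, progression HR 1.5): 68% v 69%.
- Moderate (size HR 1.5–1.8, progression HR 2 in 30%): 63–64% v 70–74%.
- Strong (size HR 1.8, progression HR 2.5 in 40%): 64% v 80%.

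**3. Type I error.** At 60% control FFLP and a true HR of 1, the log-rank test rejects in 5.2%, 4.5% and 5.2% of trials for covariate HRs of 1.3, 1.5 and 2.0. The adjusted Cox model rejects in 4.8%, 5.1% and 5.5%.

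**4. Effect on an unadjusted hazard ratio.** At 60% control FFLP and HR 0.5, the mean unadjusted HR over all trials is 0.51, 0.52 and 0.56, against 0.49 adjusted. Being nearer to 1 on average mostly reflects a marginal v a conditional hazard ratio, which is not bias. In the 12–13% of trials where progression at entry is at least 10 points commoner in the SABR arm, the unadjusted mean moves to 0.53, 0.57 and 0.64, while the adjusted one stays at 0.49–0.50.

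**The case against.** Much of the case on the other side stands.

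- **The log-rank test is not wrong.** An unadjusted log-rank is an accepted primary test in a randomised trial. Its error rate already allows for chance imbalance, and the simulations confirm about 5%. A reader who infers that the primary test is biased or invalid goes too far.
- **Imbalance need not stay in the reported hazard ratio.** A reader might infer that it does, but the article also plans a multivariate Cox model and the reported ratio may come from it. The remark applies to the log-rank comparison and to any unadjusted ratio. A covariate list is commonly left to a fuller document, so its absence here is not the point. The point is that the one comparison the article names is unadjusted.
- **The article does not say that baseline tests are how imbalance will be handled.** It lists them without stating a use, and it speaks of demographic data, so initial response and size may not be among the variables tested. That covariates would be chosen from those p values is inference.
- **The size of the gain is assumed.** The article says that size affects treatment, not that it predicts FFLP. With weak predictors the gain is within or near simulation error.
- **A single 10-point gap is modest.** With 30% progressing and HR 2, an adverse gap moves the mean unadjusted HR from 0.51 to 0.55. On the log scale that is ln(0.55/0.51) = 0.076, about a quarter of the standard error of 0.29. Power falls from 65% to 55%, but only in the adverse direction, whereas the 17–26% above counts both.
- **Progression after TACE is not always growth of the treated tumour.** Primary outcome measure lets new lesions count as progressive disease, while FFLP counts in-field progression only. A covariate built on overall response could predict FFLP less well than simulated. This is right, and it changes the fix.
- **Wide variation in size is inferred.** Entry is limited to BCLC A–B and stratified on it, which may partly balance tumour burden.

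None of this removes the core: two plausible predictors of a local endpoint are available at entry, and the named primary comparison uses neither.

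**Conclusion.** A cheap improvement, not an error of validity. The test named for FFLP is an unadjusted log-rank, and the status and content of the Cox model are left open. Adjusting for treated-lesion response and size would raise power by about 1–3 points if they are weak predictors, 3–10 if moderate and 9–20 if strong. It would also keep chance imbalance in them out of the primary estimate.

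These figures rest on 60 per arm, a conditional HR of 0.5, two-year follow-up and assumed prognostic strengths, control FFLP and loss to follow-up. The simulations adjusted for response and size only and did not model the BCLC and bilirubin strata. The direction was the same in every scenario; only the size depends on the assumptions.

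**What to change.** Name as the primary FFLP comparison the treatment term of a Cox model with a short covariate list, fixed before any outcome data are compared by arm:

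- treated-lesion response to the initial TACE, progression v partial response or stable disease, judged on the target lesion and not on new lesions elsewhere;
- log of the largest target-lesion diameter on the screening scan;
- the two randomisation factors, BCLC stage (A v B) and total bilirubin in its two stratification bands.

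Keep the log-rank test as a supportive analysis. State that the primary hazard ratio and its 95% confidence interval come from the adjusted model. Replace the chi-square and Wilcoxon tests of baseline data with a descriptive table by arm.

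The change is to analysis wording and needs no new visits, scans or patients; response has to be recorded at the level of the treated lesion. There are two small downsides. The hazard ratio becomes conditional on the covariates and should be described so. The model has five coefficients including treatment: with about 50 events that is 50/5 = 10 events per coefficient, and with about 40 events it is 8, so the list should not grow further.
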